#### Study hypotheses and outcomes

We hypothesise that participants receiving the *HeadGear* intervention will have reduced levels of depression symptomatology at post-intervention and 3-month follow-up, compared to participants in the attention-matched control condition. While the primary analyses will be conducted on the entire sample (to examine the intervention effect). We also predict the intervention effect to vary according to the level of depression symptoms at baseline [56], with a greater effect amongst those with higher levels of symptomatology.

Secondly, it is hypothesized that—relative to the control group—*HeadGear* Intervention participants will have lower rates of depressive disorder as detected by the PHQ algorithm at all follow-up time points. We also hypothesise that the intervention group will have reduced levels of anxiety symptomatology, and improved wellbeing, resilience, and work performance, at all follow-up time points, relative to controls.

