#### Secondary outcomes

A range of secondary outcomes will be considered, including change in anxiety symptomatology (as measured by the PHQ-2) at both 5-week and 3-month follow up. Other secondary outcomes include incident caseness of depression at 5-week and 3-month follow-up (as measured by the PHQ-9 diagnostic algorithm), and the level of depression symptoms (PHQ-9) at 5-week follow up. Finally, change in Wellbeing (as measured by the WHO-5) and change in occupational functioning (as measured by the HPQ and sickness absence questions) at both 5-week and 3-month follow-ups will be outcomes of interest.

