### Statistical analysis

#### Analysis plan

Primary analyses will be undertaken on an intent-to-treat basis, including all participants as randomised, regardless of treatment received or withdrawal from the study. Likelihood based methods (mixed-model repeated measures (MMRM)) methods will be favoured to analyse change in the primary outcome measure (PHQ-9). A priori planned comparisons of change from baseline across the 3-month follow up period will be used to test the primary hypothesis. An unstructured variance-covariance matrix will be used to accommodate relationships between observations at different occasions. Variables found to be substantially imbalanced between groups post randomisation will be tentatively included in these models and retained if statistically significant and influential on outcomes. Similar analyses of scaled secondary measures will assess differential change due to intervention arm. Mathematical transformation or categorisation of raw scores may be undertaken to meet distributional assumptions and address any violation of assumptions attributable to outliers.

Baseline characteristics will be used to define subgroups that would be the targeted if the app were offered as treatment. Group membership will be used for models to evaluate moderation of effectiveness by adding appropriate interaction terms and undertaking planned comparisons. The effect on outcome of level of baseline depressive symptom levels, level of functional improvement and recruitment method at baseline will be explored using an analysis of covariance approach using baseline measures as a covariate and including a covariate by intervention arm interaction term in models. The effectiveness of the active intervention at clinically relevant levels of baseline covariates will be assessed using planned comparisons while the lowest values of covariates associated with a significant benefit of the intervention will be established using a Johnson and Neyman [57] approach.

All tests of treatment effects will be conducted using a two-sided alpha level of 0.05 and 95% confidence intervals.

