#### Sample size

As a treatment, the size of the effect of the intervention is anticipated to be moderate. Meta-analysis of previous trials of internet and mobile based treatment of depression showed a large effect size of g = − 0.90 [22]; however unguided interventions typically show smaller effect sizes. Power calculations were carried out using the R package simR [58]. Power was set at 80%, alpha at 0.05, 2-tailed tests, and a correlation of .50 between pre- and post- intervention scores was assumed. Based on these calculations, a sample size of 266 per group was needed (total *N* = 532). A conservative dropout rate of 40% at follow-up was estimated. An initial sample of 851 will therefore be recruited for the trial.

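### The moderation plan names functional improvement, which exists only after randomisation, as a baseline covariate, and its Johnson-Neyman search for a benefit threshold is not tied to a significant interaction

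*Protocol article*

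**What the plan says.** All of the moderation text is in the Analysis plan of the protocol article. It opens with the purpose: "Baseline characteristics will be used to define subgroups that would be the targeted if the app were offered as treatment". It then names the moderators, "level of baseline depressive symptom levels, level of functional improvement and recruitment method at baseline will be explored", and the model, "using an analysis of covariance approach using baseline measures as a covariate and including a covariate by intervention arm interaction term in models". Comparisons at chosen levels of the baseline covariates follow, and then the threshold search: "the lowest values of covariates associated with a significant benefit of the intervention will be established using a Johnson and Neyman" approach. The only error level given is general: "All tests of treatment effects will be conducted using a two-sided alpha level of 0.05 and 95% confidence intervals".

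Two other sections bear on this. Secondary outcomes states that "change in occupational functioning (as measured by the HPQ and sickness absence questions) at both 5-week and 3-month follow-ups will be outcomes of interest". Study hypotheses and outcomes predicts improved work performance in the app arm and, for baseline depression only, a direction of moderation: "with a greater effect amongst those with higher levels of symptomatology". Table 1 shows the HPQ collected at baseline and at both follow-ups.

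**The concern.** There are two separate problems.

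First, one of the three named moderators cannot exist when the plan says it is measured. Improvement is a difference between a follow-up value and a baseline value. If it were entered as a covariate with an arm interaction, the model would condition on a variable that the trial itself hypothesises the app will change. The arm effect would then no longer be a randomised comparison.

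Second, a Johnson-Neyman boundary marks where the confidence interval for the arm effect stops excluding zero. That interval widens away from the centre of the covariate, so a boundary appears even when everyone benefits equally. Searching the whole covariate range at 5% per point also gives more chances of a false finding than one test does. Because baseline severity is predicted to matter, a spurious lower cut-off would look like confirmation, and a reader could take it as evidence that people below it do not benefit.

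**Working it through.** **Side by side.** The Analysis plan treats functional improvement as one of its baseline covariates. Secondary outcomes places change in occupational functioning at 5 weeks and 3 months. The two cannot describe the same kind of variable, so the named moderator is wrong as written.

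**Inputs from the article.** Two-sided alpha 0.05; 266 per group (532 in total); from Sample size, "Power was set at 80%, alpha at 0.05, 2-tailed tests, and a correlation of .50 between pre- and post- intervention scores was assumed". No numerical effect size is given. By n = 2(1.96 + 0.84)²/d², 266 per group implies d = 2.80 × √(2/266) = 0.243, or 0.243 × √(1 − 0.5²) = 0.210 if the calculation was an ANCOVA. The 0.24 used below is therefore an inferred figure, not one the article states.

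**Literal reading of improvement.** Let the app change PHQ-9 by −δ and function by +δ, in residual SD units, with correlation c between improvement in function and lower PHQ-9. The arm coefficient at average improvement is then −δ + cδ = −δ(1 − c). With δ = 0.24:

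| c (assumed) | adjusted effect | share of truth |
|---|---|---|
| 0.3 | −0.17 | 70% |
| 0.5 | −0.12 | 50% |
| 0.6 | −0.10 | 40% |
| 0.7 | −0.07 | 30% |

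Simulation (n = 532) gave −0.166, −0.122 and −0.073 at 0.3, 0.5 and 0.7. If the app changes function by 0.24 but does not change PHQ-9, the adjusted effect at c = 0.5 is 0 + 0.5 × 0.24 = +0.12, an apparent harm where none exists.

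**Johnson-Neyman, the plan's own level first.** The ANCOVA with interaction was simulated under no effect and no moderation (n = 532, r = 0.5, 10,000 runs per setting). Tested at one fixed value, the covariate mean, the arm effect was significant in 4.8-5.4% of runs, so the stated 5% is reproduced.

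**Ungated search, no effect anywhere.** At each covariate value x, t(x) = (b₁ + b₃x)/√(V₁₁ + 2xV₁₃ + x²V₃₃), where b₁ is the arm term, b₃ the interaction and V their covariance matrix. It is compared with 1.964. Over an unlimited range the either-direction rate is P(χ² on 2 df > 1.96²) = exp(−1.92) = 14.65%. Over realistic ranges, for one continuous covariate:
- significant region in either direction: 13.5-14.8%, against 5%;
- benefit region: 7.3-8.3%, against 2.5% for that direction.

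Across three moderators (two continuous, one binary), the rates are 24-26% and 14-15%.

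**Ungated search, constant effect.** With the same true benefit at every covariate value, sized for 80% power, a threshold inside the covariate range appeared in 82-85% of runs, depending on how much of the range was scanned.

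**With an interaction test at 5% first.** Under the null, a region in either direction appeared in 4.3-5.0% of runs and a benefit region in 2.6-3.7%. Under the constant effect, a region was reported in about 5.3%.

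**With a simultaneous critical value instead.** √5.99 = 2.45, and exp(−5.99/2) = 5%, so the null rate is held. It does not remove thresholds under a constant effect. At 80% power the expected z at the covariate mean is 1.96 + 0.84 = 2.80, so 2.45 is exceeded there with probability Φ(2.80 − 2.45) = Φ(0.35), about 64%. The bound also makes it harder to reach significance away from the mean, so a boundary still appears.

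**The case against.** The strongest reply on the covariate is that the Analysis plan labels these variables as baseline three times: in the list, in the model description and in the sentence on planned comparisons. A reader might infer that the authors mean to adjust for a post-randomisation result. The text points the other way, and a slip for baseline function or impairment is the more natural reading. That stands, so the attenuation figures describe only the literal reading. The wrong variable is still named, and a later analyst could follow the words.

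On Johnson-Neyman, the article never says that the test is pointwise or ungated. It mentions interaction terms, calls this work exploratory, and may leave the details to an analysis plan that is not shown. This also stands, and it is why the rates above are conditional. The article does, however, fix the search rule and the alpha level, and the constant-effect result shows that the missing condition matters.

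Three further inferences are tempting but not supported:
- That a false benefit threshold arises far more often than 5%. For one covariate it is 7-8%: about three times the 2.5% for that direction, but only about 1.5 times 5%. The 13-15% also counts regions of harm, which the rule does not seek.
- That these models drop participants with missing follow-up. The article speaks of an analysis of covariance approach and nowhere restricts it to completers. A baseline covariate and its interaction fit equally well in the mixed model, and the Discussion relies on methods robust to data missing at random.
- That the Johnson-Neyman boundary will decide who is offered the app. The article says that baseline characteristics define the subgroups to be targeted; it does not give the boundary that role.

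**Conclusion.** The point holds in two parts, and neither touches the primary analysis. The named moderator is wrong as written, because functional improvement cannot be a baseline covariate. It is probably a slip; used literally, it would cut the arm effect to roughly 70%, 50% or 40% of the truth under an assumed 0.24 SD effect on both outcomes and assumed correlations of 0.3, 0.5 and 0.6.

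The Johnson-Neyman rule is under-conditioned. If it is applied pointwise and without an interaction test, one continuous covariate yields a significant region in about 13-15% of null trials and a benefit region in about 7-8%. When everyone benefits equally, it yields a threshold in over 80%. The last figure matters most, since it shows that the rule would usually produce a cut-off without any moderation.

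These rates assume normal residuals, a 50:50 binary recruitment method, and an assumed covariate distribution. Normal, truncated normal on 9-27 and uniform on 15-27 gave similar results.

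**What to change.** 1. Replace functional improvement with a named, measured baseline variable, such as baseline HPQ work performance. Table 1 already collects it, so no new data are needed.
2. State that a Johnson-Neyman region is reported only if the arm-by-covariate interaction is significant at 5%, only within the observed baseline range, and labelled exploratory. A simultaneous critical value of about 2.45 also controls the null rate, but does not by itself stop false thresholds under a constant effect. Requiring both is not necessary.
3. Optionally, say that the interaction is fitted within the mixed model, which would settle how incomplete follow-up is handled.

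The change is to wording only. The price is fewer or narrower regions of claimed benefit, including some trials in which real moderation goes unreported because the interaction test lacks power.

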#### Sample size

As a treatment, the size of the effect of the intervention is anticipated to be moderate. Meta-analysis of previous trials of internet and mobile based treatment of depression showed a large effect size of g = − 0.90 [22]; however unguided interventions typically show smaller effect sizes. Power calculations were carried out using the R package simR [58]. Power was set at 80%, alpha at 0.05, 2-tailed tests, and a correlation of .50 between pre- and post- intervention scores was assumed. Based on these calculations, a sample size of 266 per group was needed (total *N* = 532). A conservative dropout rate of 40% at follow-up was estimated. An initial sample of 851 will therefore be recruited for the trial.

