## Methods

### Design

The aim of the current study will be achieved through a multicentre randomized controlled trial, with two parallel arms. The trial will compare two smartphone app-based interventions: a novel intervention app designed for the treatment of depression (Headgear) and an attention control app (mood monitoring). Assessments will occur at baseline, post-intervention (5-weeks), and at 3-month follow-up. The study is registered with the Australian New Zealand Clinical Trials Registry (ACTRN12617000547347) and has ethical approval from the University of New South Wales (UNSW) Human Research Ethics Committee (HC17021). Consent to participate in the trial will be obtained electronically from all participants. The study will be conducted in accordance with the Helsinki Declaration [25] and is compliant with the CONSORT guidelines [26].

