### Setting and participants

The study will recruit Australians who are currently employed, and will sample more selectively from a range of male-dominated industries [27]. In Australia, these industries include agriculture/forestry/fishing, utility services (electricity, gas, water and waste), wholesale trade, manufacturing, transport/postal/warehousing, mining, and construction [28]. Emergency services and defence also fit this definition, but were not considered unique industries by the ABS, though for this study they will also be considered as male-dominated.

Industry partner organisations will assist with recruitment by promoting the study among specific groups or their entire workforce. We will aim to recruit at least 850 employed adults across Australia. Organisations that elected to participate will promote the study via their respective health and wellbeing officers, along with email and newsletter advertisements. The study will also be promoted via members of the research team presenting at partner worksites. Social media advertising targeted at employed people will also be utilised to recruit individuals employed externally of partner organisations using an evidence-informed advertising approach [29]. Both males and females will be recruited.

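### The recruitment target of 851 does not follow from 532 participants needed and 40% dropout; it leaves about 255 per group rather than 266, and about 78% power on a completers-only basis

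*Protocol article*

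**What the plan says.** The Sample size section gives the design inputs: "Power was set at 80%, alpha at 0.05, 2-tailed tests, and a correlation of .50 between pre- and post- intervention scores was assumed". It continues: "Based on these calculations, a sample size of 266 per group was needed", which it totals as 532. It then allows for attrition: "A conservative dropout rate of 40% at follow-up was estimated. An initial sample of 851 will therefore be recruited for the trial". The Setting and participants section repeats the target in rounded form: "We will aim to recruit at least 850 employed adults across Australia".

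The effect behind the calculation is described only in words: "the size of the effect of the intervention is anticipated to be moderate". The same paragraph contrasts this with a meta-analytic g of −0.90, which it calls large, and notes that unguided interventions tend to do less well. The power calculation was done by simulation with the R package simR. The effect, variance components and number of occasions entered are not shown.

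The Analysis plan section specifies a likelihood-based mixed model for repeated measures (MMRM) on everyone randomised. Table 1 schedules the PHQ-9 at baseline, 5 weeks and 3 months. The primary outcome is the 3-month score.

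**The concern.** The paragraph presents 851 as the result of two inputs, 532 needed and 40% lost, yet those inputs give a different number. No other inflation rule or dropout rate appears in the article, and the second mention of the target only repeats it. The sample size paragraph therefore claims 80% power at 40% dropout when its own figures do not deliver that.

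The allowance also carries some weight in the argument. The Discussion lists attrition as an expected limitation and offers the cautious dropout estimate as one of the reasons it should be contained.

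A second, looser matter is that a power statement is hard to interpret without its effect size. Here the verbal description of the effect does not sit easily beside the number per group.

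**Working it through.** **Inputs, all from the Sample size section unless noted**

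- Needed per group: 266; total 532.
- Dropout: 40%.
- Stated target: 851.
- Two-sided alpha 0.05, power 80%, pre-post correlation r = 0.50.
- Two parallel arms (Design section), of equal size as the per-group figure implies.
- Effect size: not stated numerically.

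**Step 1. Try to reproduce 851**

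- Standard inflation, N/(1 − d): 532/0.60 = 886.7, so 887 (or 888, 444 per group, with equal arms). This is not 851.
- The common slip, N × (1 + d): 532 × 1.4 = 744.8, so 745. This is not 851.
- 532 × 1.6 = 851.2. This matches numerically.
- Solving 532/(1 − d) = 851: d = 1 − 532/851 = 0.375. This matches numerically too, but it is not the stated dropout.

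The stated inputs do not reproduce 851. Two routes reach it, and the article does not say which, if either, was taken.

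**Step 2. What 851 leaves at 40% dropout**

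- 851 × 0.60 = 510.6, about 511 in total and about 255 per group.
- Shortfall: 532 − 511 = 21 participants with 3-month data, about 11 per group.
- Expressed as randomised participants: 887 − 851 = 36; 36/851 = 4.2%.
- For the rounded target of 850: 850 × 0.60 = 510, again 255 per group.

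**Step 3. Power at 255 per group**

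Power is Φ(δ√(n/2) − 1.960), where δ is the standardised effect. Take the effect that gives 80% at n = 266, so that δ√(266/2) = 1.960 + 0.842 = 2.802. At n = 255:

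- 2.802 × √(255/266) = 2.802 × 0.979 = 2.743
- 2.743 − 1.960 = 0.783
- Φ(0.783) = 0.783

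Power is about 78.3%, and a noncentral t calculation gives the same figure. Only the ratio 255/266 enters, so the result does not depend on the unstated effect, the standard deviation or r.

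**Step 4. Effect implied by 266 per group (secondary point)**

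Use a simple two-sample formula with the stated alpha, power and r:

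- Post-score contrast, or change score (with r = 0.50 the change-score SD equals the raw SD): 2.802 × √(2/266) = 0.243.
- Baseline-adjusted: 0.243 × √(1 − 0.50²) = 0.243 × 0.866 = 0.210.

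For scale, by the same formula:

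| Standardised effect | n per group, unadjusted | n per group, baseline-adjusted |
|---|---|---|
| 0.3 | 175 | 131 |
| 0.4 | 99 | 74 |
| 0.5 | 63 | 48 |

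These are back-calculations. They do not reproduce the simulation, whose inputs are not given.

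**The case against.** The strongest reply concerns size, not arithmetic. The loss is about 1.7 percentage points. The target covers dropout up to 37.5%, only 2.5 points below a rate that the authors themselves regard as cautious. The rounded target is worded as a minimum. The 266 came from simulation. If 1,000 runs are assumed (the number is not stated), the 95% Monte Carlo margin around 80% is 1.96 × √(0.8 × 0.2/1000) = 2.5 points, wider than the shortfall. All of this stands and keeps the point minor. None of it makes 851 follow from 532 and 40%.

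The second reply is that 78.3% is not the power of the planned analysis. The MMRM also uses participants who are missing at 3 months but seen at 5 weeks. This stands as well, although recovery is not assured. Take 255 seen and 170 missing per group at 3 months, and let ρ be the baseline-adjusted correlation between the two follow-ups. The variance factor is then (1 − ρ²)/255 + ρ²/(255 + m), where m is the number seen at 5 weeks only. Setting it equal to 1/266:

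- If all pairwise correlations are 0.50, ρ = (0.50 − 0.25)/0.75 = 1/3, and m must be about 151, or 89% of the 170.
- If ρ = 0.5, m must be about 50, or 30% of the 170.

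So 78% is an approximate lower figure. The Sample size section does, however, treat 532 as the number required after dropout, and on that basis its inflation step fails.

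Two stronger readings are tempting, and the article supports neither. A reader might infer that the authors multiplied by 1.6 by mistake. The match is close, but the derivation is not shown and a 37.5% dropout figure fits equally well. A reader might also infer that 80% power and a moderate effect are incompatible. That depends on an outside convention that moderate means 0.5, a value the article never gives. It also depends on a two-sample formula standing in for a simulation whose inputs are not visible. The same paragraph says that unguided interventions usually have smaller effects.

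**Conclusion.** The point holds as a minor correction. The stated target is inconsistent with the stated requirement and dropout: 887 would be needed, and 851 yields about 255 per group. Completers-only power is about 78% instead of 80%, given equal arms, exactly 40% loss at 3 months and the document's own 80% at 266 per group. Any MMRM recovery would raise that figure by an amount the article does not allow one to calculate. The trial's conclusions are not threatened.

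Confidence in the inflation arithmetic is high. Confidence in the effect-size remark is lower: an implied effect of about 0.21 to 0.24 sits awkwardly with the word moderate. That justifies asking for the number used, and does not justify calling the statement contradictory.

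**What to change.** Reword the Sample size paragraph and leave recruitment unchanged. Either of these would do:

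- State that 851 randomised with 40% dropout leaves about 255 per group at 3 months and about 78% power, before any gain from 5-week data in the MMRM.
- State that 851 randomised preserves 266 per group, and so 80% power, for dropout up to 37.5%.

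Keep the rounded target in Setting and participants consistent with whichever is chosen; at exactly 850 the dropout limit is 1 − 532/850 = 37.4%. Beside the power figure, give the standardised effect actually entered in simR, taken from the simulation code and not from the back-calculation above.

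The cost is one edited paragraph and a slightly less favourable power or dropout statement. No further participants and no change to the analysis are needed.

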The proposed trial does carry with it a number of limitations. The use of a smartphone app as a delivery modality does mean that the intervention is unguided and that the user is responsible for managing their interaction with the program. Thus, trial attrition and disengagement are expected issues [64, 65]. It is worth noting, however, that this has also been an issue for face-to-face psychotherapy trials [66]. The reason for drop out in both mhealth and face-to-face trials is often multi-faceted, and whilst can be related to engagement with the program, it is rarely only due to dissatisfaction [67].To account for potential drop out, two procedures were put into place. Firstly, all follow-up communication would occur via phone numbers to ensure that if the participant uninstalled the app before the follow-up period, the participant could still be reached. Secondly, conservative drop-out estimation and the use of statistical methods robust to data missing at random, it is believed that this limitation will be minimised.

Another limitation of the present trial is related to the reliance on self-reported depressive symptoms, rather than a diagnosis of depression achieved through a structured diagnostic interview. This is a common issue faced by most similar trials given the constraints around time and resources. To overcome this issue, we will use a well-validated measure (PHQ-9) that contains two methods for classifying depression: 1) threshold total score above 14 (sensitivity = 67%; specificity = 95%) [68] or 2) meeting the depression algorithm’s criteria (sensitivity = 0.53; specificity = 0.94) [69]. By using both methods, we are confident that participants without significant symptomatology will be excluded and those with significant symptomatology will be included.

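### The recruitment target of 851 does not follow from 532 needed and 40% dropout: it covers about 37.5%, and 40% would require 887

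*Protocol article*

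**What the plan says.** The Sample size section of the protocol article sets out the calculation in a few lines. The design values are given as "Power was set at 80%, alpha at 0.05, 2-tailed tests", which agrees with the Analysis plan section: "All tests of treatment effects will be conducted using a two-sided alpha level of 0.05 and 95% confidence intervals". The expected effect is described in words only ("the size of the effect of the intervention is anticipated to be moderate"), and "a correlation of .50 between pre- and post- intervention scores was assumed". From these the section concludes that "a sample size of 266 per group was needed", giving a total of 532.

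The dropout step follows directly: "A conservative dropout rate of 40% at follow-up was estimated. An initial sample of 851 will therefore be recruited for the trial".

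Two other places use the result. Setting and participants gives the target as a rounded minimum: "We will aim to recruit at least 850 employed adults across Australia". The limitations part of the Discussion names attrition as an expected problem and answers it partly with "conservative drop-out estimation and the use of statistical methods robust to data missing at random".

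**The concern.** The word linking the dropout rate to the target presents 851 as derived from 532 and 40%. The three figures cannot all stand. If 40% of 851 people are lost, fewer than 532 remain. If 532 must remain, either more than 851 must be recruited or dropout must stay below 40%. No other section gives a different dropout rate, a different inflation rule or another reason for 851.

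The credibility of a printed sample size justification is at stake. A reader with a calculator can see that the recruitment target falls short of its own inputs. The Discussion leans on the same allowance as protection against attrition, so the text should state correctly how much dropout the target absorbs.

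**Working it through.** **Inputs**, all from the Sample size section unless noted:
- required number: 266 per group, 532 in total
- dropout at follow-up: 40%, read here as loss by the 3-month primary time point
- recruitment target: 851 (at least 850 in Setting and participants)
- power 80%, two-sided alpha 0.05
- pre-post correlation 0.50
- effect size: no number given

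**Reproducing the plan's figures**
- 2 x 266 = 532. Reproduced.
- Standard inflation, n / (1 - d): 532 / 0.60 = 886.7, so 887 (888 with equal arms, 2 x 444). This is not 851.
- Common shortcut, n x (1 + d): 532 x 1.40 = 744.8, so 745. This is not 851 either.
- 532 x 1.60 = 851.2. This matches 851. It uses the retention share, 0.60, as an add-on. That this step was taken is inferred from the match alone.

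**What 851 delivers**
- Retained at 40% dropout: 851 x 0.60 = 510.6, or 255.3 per group.
- Shortfall: 532 - 510.6 = 21.4, and 21.4 / 532 = 4.0%.
- Dropout that 851 absorbs: 1 - 532/851 = 0.375.
- Extra recruits needed for 40%: 887 - 851 = 36 (37 with equal arms).
- The rounded target behaves the same way: 850 x 0.60 = 510.

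**Completer-based power**

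The 266 per group cannot be checked without a numerical effect size, but the loss of power can be found without one. Take whatever effect gives 80% at 266 per group. With the normal approximation, power at n per group is

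Φ[(1.960 + 0.842) x √(n/266) - 1.960].

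- n = 266: Φ(0.842) = 80.0%.
- n = 255.3: √(255.3/266) = 0.980, so Φ(2.745 - 1.960) = Φ(0.785) = 78.4%.
- n = 255: 78.3%.

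The effect this implies at 266 per group is 2.802 x √(2/266) = 0.243 SD. That holds for an unadjusted comparison, or for change scores with r = 0.50, whose variance factor 2(1 - r) equals 1. For a baseline-adjusted comparison it is 0.243 x √0.75 = 0.210 SD. The smallest effect detectable with 80% power rises by a factor √(266/255.3) = 1.021, about 2%.

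**The case against.** The arithmetic is hard to dispute. The case on the other side concerns what it implies, and most of that case stands.

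**Power.** A reader might infer that the trial will not have its stated 80% power. The document does not support that as a flat statement. The 78% counts completers only, whereas the Analysis plan specifies intention to treat with a likelihood-based repeated-measures model. Randomisation follows the baseline assessment, so dropouts still contribute a baseline score and some will have a 5-week score. How much this returns depends on details the article does not give:
- Suppose the 266 came from change scores with r = 0.50, baseline enters the model as a response, and data are missing at random. The variance is then proportional to 0.25/851 + 0.75/510.6, an effective total of about 567. That exceeds 532, and power is about 82% even without 5-week data.
- Suppose the 266 came from a baseline-adjusted comparison. Baseline scores of dropouts then add nothing of this kind, and about 78% stands unless 5-week data help. Assuming 70% retention at 5 weeks (595.7 people) and a correlation of 0.6 between follow-ups, the variance is proportional to 0.64/510.6 + 0.36/595.7. The effective total is about 538, with power close to 80%. Neither assumed value is in the document.

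So some or all of the loss may be recovered. This does not rescue the derivation, because the Sample size section neither states nor relies on such a gain.

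**The word conservative.** A reader might also infer that the dropout estimate is not conservative. That does not follow. In both the Sample size section and the Discussion the word describes the assumed rate, and the inflation step says nothing about whether 40% is a cautious forecast.

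**The figure of 850.** A minimum of 850 is compatible with either 851 or 887, so it is not a separate contradiction.

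**Conclusion.** The point holds as a minor arithmetic error. The 851 does not follow from 532 and 40% dropout. It covers about 37.5%; at 40% it leaves about 510 people, 21 to 22 short (4%), and 887 would be needed. This rests only on the three printed figures and on reading the rate as the share of recruits lost. It does not depend on how 851 was reached, so the multiplication by 1.60 should be described only as the apparent source.

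The consequence for power is at most modest. On a completer basis it is about 78% instead of 80%, a loss of under 2 percentage points. The trial's actual power under the planned mixed model cannot be settled, because the article gives neither a numerical effect size nor the model that was simulated. The supportable claim is that 851 does not preserve 532 completers at the stated dropout rate; a claim that the trial is underpowered would go beyond the document.

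**What to change.** Keep recruitment as planned and correct the dropout sentence in the Sample size section in one of two ways:
- state that recruiting 851 allows for 37.5% dropout while keeping 532; or
- state that 851 recruited with 40% dropout leaves about 510 (about 255 per group), with completer-based power of about 78%.

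In either case, add that 40% dropout would require 887 recruits (532 / 0.60). If the authors wish to rely on the mixed model to make up the difference, the section should say so and give the assumptions.

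The word conservative can stay as a description of the 40% rate. The minimum of 850 in Setting and participants needs no correction; aligning it with the restated figure is optional tidying.

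The cost is a sentence or two of wording. No extra participants and no change to design or analysis are required, and one stated figure becomes slightly less favourable.
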